**Amendment 2**

The following amendment is proposed, as of 24/09/2018:

Investigators

The research team would like to add statisticians [name], [name], [name] and [name] to the project.

Objectives

We wish to update Objective 5:

1. To determine patterns of multimorbidity disease combinations associated with health service utilisation outcomes, treatment burden, mortality, index of multiple deprivation and age in order to identify clusters of patients that are in some respect “similar.”

Data Linkage Required (if applicable)

To assess the relationship between multimorbidity clusters and mortality, we additionally wish to link ONS mortality data.

Data/Statistical Analysis

We propose to use profile regression (see below) instead of latent class analysis to cluster patients based on their health conditions. Formally, profile regression is a latent class analysis, with the addition that clusters are sought which are related to the outcome. As described above, we will generate clusters associated with health service usage, treatment burden (number of current prescription medications), mortality, index of multiple deprivation and age. This will ensure the clusters found are relevant to those outcomes, and so will be most useful. Rather than random effects for practices, we will study the impact of practice-level variation by adding it as a fixed effect co-variate into our model. We will perform cross-validation to ensure the robustness of our results.

**Reference for profile regression:** https://arxiv.org/abs/1303.2836

**Amendment 3**

The following amendment is proposed, as of 27/11/2019:

Data/Statistical Analysis

For the first publication on clustering of multimorbidity patients we used Latent Class Analysis, as specified in the original protocol. This will be applied in patients stratified by age (18 – 44, 45 – 64, 65 – 84, 85+ years old) to highlight the relevance of different conditions to multimorbidity at different age groups.

Outcome-guided clustering will instead form part of a second clustering paper, that is more methodological. This paper will be about the balance between inference and prediction in studies where we are interested both in clustering and in outcomes. We have already compared various methods on simulated data, and now would like to demonstrate their effect on real data.

There are three quantities of interest: patient cluster (C), cluster-specific outcome (Y|C where Y=outcome, say mortality), patient-specific outcome (Y|U or Y where U = a vector of conditions a patient has). Ideally we want estimates for all quantities to be accurate, but essentially this leads to the dream of getting both inference (correct C, correct Y|C) and prediction (Y) right; i.e. we aim to uncover the true data-generating mechanism such that prediction is naturally accurate. The problem here is that by introducing cluster (C), we are likely to introduce extra uncertainty in the model such that we may deviate more from a prediction goal.

The methods we will compare are:

- The most popular approach, and the one we have taken so far, called the modal-class approach, where clusters are learned first (based on the vector of conditions a patient has U) and compared to outcomes post-hoc.
- The 1-step approach, with simultaneous estimation of clusters and the relationship with outcomes, assuming conditional independence between indicators (Us) and outcome (Y).
- 1-step local dependence-corrected approach, which takes local dependence into account using a restricted/non-restricted latent factor structure
- Bias-corrected 3-step approach: Recognise misclassification error in the modal-class approach and introduce “misclassification weights” to correct for biased Y|C relationship.
- Regression: Us are included as predictors of Y.

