To meet our fifth aim of determining patterns of multimorbidity associated with health service utilisation outcomes, we will use a latent class analysis (Hagenaars *et al.* 2002) to classify patients according to their distribution of multimorbidities^25^. Within each class of patients, we will assume a distinct multivariable model of health service utilisation outcome. This approach will assist in the identification of class specific factors associated with health service usage. Ideally, we want to fit models including random effects to allow for variation between practices. Depending on the number of classes obtained, this could potentially be quite a big model with a large number of parameters. If appropriate, we will investigate sub-sampling methods for this data set, choosing a suitable representative sample on which to run the chosen models^26^.

1. **Plan for addressing confounding**

*Purely descriptive studies are exempt from this requirement. All other studies should here provide some discussion of what they are doing in the design and/or analysis to control for confounding.*

We will adjust for confounding using multivariable regressions with random-effects models to account for age, sex, socioeconomic deprivation, ethnicity, smoking status, and region, as well as for clustering by GP practice.

1. **Plan for addressing missing data**

*The potential for missing data should be identified and how it will be addressed discussed here.*

We will only use patients with complete age, gender, and IMD data. To reduce the proportion of patients with missing IMD data, we will only use linked practices. Patterns of missingness in the data set will be described and explored at an early stage, and we will consider using multiple imputation techniques where appropriate^27,28^. Missing data for smoking status will be imputed using the last observation carried forward method.

1. **Limitations of the study design, data sources and analytical methods**

*The general limitations of the databases and observational research are well-known. Specific consideration of the potential impact of such limitations should be provided in the context of the proposed study.*

The key limitations to this protocol are as follows:

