**Amendment 4**

The following amendment is proposed, as of 5/12/2019:

Our application of latent class analysis in age strata to determine multimorbidity clusters has revealed many clusters which we wish to understand better.

Data/Statistical Analysis

Subsequent to the identification of clusters of multimorbid patients using latent class analysis and a list of ~40 conditions, we wish to further characterise these clusters in the following ways:

1. Describing **the prevalence of 308 fine-grained conditions** within these clusters (e.g. prevalence of lung cancer, not just cancer). This will be a descriptive analysis using the 308 conditions defined here: <https://www.caliberresearch.org/portal/phenotypes/chronological-map>
2. **Which conditions are recorded first?** Our existing clusters are based on the prevalence of conditions in 2012, defined in the following way: <https://www.phpc.cam.ac.uk/pcu/cprd_cam/codelists/v11/> . We will begin with a simple descriptive analysis of which diseases within a cluster are (on average) recorded first. After this we may try and calculate for each cluster pairs of conditions (A and B) where A more often comes after B, and the relative risk of B given A happening earlier using the approach of Jensen et al., (2014) Nat Comm.
3. **Which causes of death are associated with each cluster?** We will use perform a descriptive analysis of primary cause of death for each cluster
4. **Can we improve identification of multimorbid individuals through the use of linked HES data?** While we have used HES linkage to look at hospitalisation, we have not used it to identify the diseases an individual has. This made sense from the point of view of studying the GP perspective on multimorbidity, but there will be some patients who receive diagnoses in secondary care that do not get entered into GP records. We will use existing HES definitions from <https://www.caliberresearch.org/portal/phenotypes> . We will assess the prevalence of each of the broad disease areas (from the original protocol) and whether it increases with the addition of HES-only diagnoses. We may also repeat the Latent Class Analysis to see how/if results change.

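### The Aim 5 cluster–outcome comparison rests on modal-class assignment, which Amendment 3 itself says gives a biased relationship, while the listed correction is kept for a second, methodological paper

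*Protocol*

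**What the plan says.** Four places bear on how clusters are linked to outcomes.

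- **Data/ Statistical Analysis, fifth aim.** Latent class analysis is used "to classify patients according to their distribution of multimorbidities". Then: "Within each class of patients, we will assume a distinct multivariable model of health service utilisation outcome". Only service use is named as an outcome, and it is not said whether classes and outcome model are fitted jointly or in sequence.
- **Amendment 2.** Aim 5 now seeks disease patterns "associated with health service utilisation outcomes, treatment burden, mortality, index of multiple deprivation and age". The method changes: "We propose to use profile regression (see below) instead of latent class analysis to cluster patients based on their health conditions".
- **Amendment 3.** For the first clustering publication "we used Latent Class Analysis, as specified in the original protocol", stratified by age. Outcome-guided clustering moves to a second, more methodological paper. In the list of methods for that paper, the modal-class approach is identified as the one taken so far, in which "clusters are learned first (based on the vector of conditions a patient has U) and compared to outcomes post-hoc". A bias-corrected 3-step approach is listed, whose weights serve "to correct for biased Y|C relationship". Also listed are a 1-step approach that assumes conditions and outcome are independent given class, and a version that allows for local dependence.
- **Amendment 4.** The clusters are to be characterised further, by the prevalence of 308 fine-grained conditions (item 1) and by cause of death: "Which causes of death are associated with each cluster" (item 3).

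**The concern.** The outcome given cluster is one of the three quantities of interest that Amendment 3 names, with mortality as its example. The plan describes its working estimator of that quantity as biased and names a remedy, but uses the remedy only in a methods comparison. The substantive answer to Aim 5 is left on the uncorrected estimator.

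Assigning each patient to the most likely class and then treating that class as known mixes patients from different true classes. A sample of 425,400 does not reduce this error; it only narrows the intervals around a displaced value. Readers who use the clusters to judge which patients carry the highest mortality or service use would see contrasts of the wrong size, and could see a difference between clusters whose true risks are equal.

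The outcome step is also left unsettled. The main text, Amendment 2 and Amendment 3 each describe a different link, and Amendment 3's reference to the original protocol clearly covers only the clustering.

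**Working it through.** **Plan's own figures.** The plan gives no number for this step. Its only calculated figure, the sample size for prevalence, reproduces: 1.96² × 0.232 × 0.768 / 0.0013² = 405,018, and 405,000 / 0.952 = 425,420. Nothing below depends on it. All class structures and risks below are assumptions, because the documents give none.

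**General form.** Let C be true class, M assigned class, U the conditions and r_c the true outcome risk in class c. M is a function of U. If the outcome is independent of U given C, then

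P(Y = 1 | M = m) = Σ_c P(C = c | M = m) · r_c.

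Each modal-class rate is a weighted average of the true rates. Apart from sampling error, the highest-to-lowest spread cannot widen, for any number of classes. Differences between other pairs can move either way.

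**Two classes, independence holds, true risks 20% and 10%.** The observed difference is 0.100 × (PPV₁ + PPV₀ − 1), where PPV is the share of an assigned class that truly belongs to it.

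| Correct assignment | Equal classes | 20:80 split |
|---|---|---|
| 95% | 0.090 | 0.081 |
| 90% | 0.080 | 0.067 |
| 80% | 0.060 | 0.044 |
| 70% | 0.040 | 0.027 |

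Example: equal classes at 90% give 0.100 × (0.9 + 0.9 − 1) = 0.080.

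**Three classes, independence holds** (simulation, N = 500,000, 10 conditions, 78% correctly assigned, entropy 0.54). True rates 0.100, 0.100 and 0.252 appear as 0.136, 0.119 and 0.209. The spread falls from 0.152 to 0.090, which is 59% of the truth. The two equal classes appear to differ by 0.017.

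**Five classes, 36 conditions.** With a true mortality spread of 0.20, the modal-class spread was 0.09 to 0.16 (0.09 / 0.20 = 45%; 0.16 / 0.20 = 80%). The misclassification correction returned 0.18 to 0.25. A separate run used 25% v 5% mortality (ratio 5.0) and class-defining odds ratios of 3, 5 and 10. It assigned 45%, 59% and 78% correctly and gave modal-class ratios of 1.7, 2.3 and 3.4, against corrected ratios of 5.4, 4.9 and 5.2.

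**Independence fails.** In a two-class simulation (10 conditions, equal classes), each extra condition added 0.03 to the risk within class. The true difference was 0.101.

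| Condition prevalence by class | Correct assignment | Modal-class difference, no direct effect | Modal-class difference, +0.03 per condition |
|---|---|---|---|
| 0.2 v 0.6 | 91% | 0.082 | 0.111 |
| 0.2 v 0.45 | 81% | 0.062 | 0.114 |

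Here the modal-class method overstates the difference.

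**What the correction does in that case.** For two classes it divides by (PPV₁ + PPV₀ − 1). With these prevalences a patient with four or more conditions is assigned to the higher class, so the factors are 0.887 + 0.941 − 1 = 0.828 and 0.859 + 0.768 − 1 = 0.626. The corrected values are 0.111 / 0.828 = 0.134 and 0.114 / 0.626 = 0.18, further from 0.101 than the uncorrected ones. In the five-class setting the correction had much the lower error even with direct condition effects. Which regime applies cannot be told from the documents.

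**The case against.** **Direction.** A reader might infer that cluster differences will be understated. The documents do not support that. Amendment 3 says the relationship is biased but gives no direction, and by listing a local-dependence method it treats the independence needed for attenuation as open to doubt. For mortality, a direct effect of individual conditions within a class is plausible. This stands.

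**Replacing the estimator.** The 3-step correction relies on the same independence and over-corrected in the two-class check. Making it the sole reported result would prejudge the comparison the second paper is meant to make. This also stands, and argues for showing both estimates.

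**Contradiction.** A reader might infer that Amendment 3 flatly contradicts the main text. It does not. The main text never says joint estimation, so classifying first and modelling within class is a fair reading. The reference to the original protocol attaches to the latent class analysis, in contrast to Amendment 2's profile regression. A later amendment may change a method, and mortality entered Aim 5 only with Amendment 2. What remains is an outcome step that the three texts leave unreconciled.

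**Already disclosed.** The plan acknowledges the limitation and will compare methods on real data. Splitting the work into two papers is legitimate, but it leaves the substantive results uncorrected.

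**Amendment 4.** Its items 1 and 3 are descriptive, and it does not say how patients are allocated to clusters. The 308 conditions overlap the clustering indicators, so the same correction would not be valid for them.

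**Conclusion.** The concern holds in a limited form. By the plan's own account, the cluster–outcome link used so far is subject to misclassification error and bias, and no correction is stated for the substantive clustering paper. The reported differences will be distorted unless classification is near perfect or errors cancel.

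If conditions and outcome are independent given class, the extreme contrasts are usually attenuated. Under the assumed five-class settings the modal-class spread was about 45–80% of the true spread. Under local dependence the contrast may be overstated, as in the two-class check (0.111 to 0.114 against 0.101). The documents do not allow the actual size or direction to be computed. A firm claim of bias towards no difference goes beyond them, as does a claim that the 3-step estimate is always nearer the truth.

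**What to change.** - In the substantive clustering paper, report the bias-corrected 3-step cluster–outcome estimates beside the modal-class ones for service use, treatment burden and mortality.
- Give classification accuracy or entropy for each of the four age strata.
- State that the correction assumes conditions and outcome are independent given class, and interpret both sets together with the local-dependence-corrected result already planned.
- In Amendment 4, do not apply this correction to the 308 fine-grained conditions. Describe those prevalences, and the causes of death, as properties of the assigned groups.
- Reconcile the fifth-aim text with Amendments 2 and 3 on how clusters are linked to outcomes, and limit Amendment 3's reference to the original protocol to the clustering step.

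The cost is wording and some extra analysis, since the methods are already on the plan's list. The downsides are wider intervals for the corrected estimates and possible over-correction if local dependence is strong, which is why both sets should be shown.

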**Amendment 4**

The following amendment is proposed, as of 5/12/2019:

Our application of latent class analysis in age strata to determine multimorbidity clusters has revealed many clusters which we wish to understand better.

Data/Statistical Analysis

Subsequent to the identification of clusters of multimorbid patients using latent class analysis and a list of ~40 conditions, we wish to further characterise these clusters in the following ways:

1. Describing **the prevalence of 308 fine-grained conditions** within these clusters (e.g. prevalence of lung cancer, not just cancer). This will be a descriptive analysis using the 308 conditions defined here: <https://www.caliberresearch.org/portal/phenotypes/chronological-map>
2. **Which conditions are recorded first?** Our existing clusters are based on the prevalence of conditions in 2012, defined in the following way: <https://www.phpc.cam.ac.uk/pcu/cprd_cam/codelists/v11/> . We will begin with a simple descriptive analysis of which diseases within a cluster are (on average) recorded first. After this we may try and calculate for each cluster pairs of conditions (A and B) where A more often comes after B, and the relative risk of B given A happening earlier using the approach of Jensen et al., (2014) Nat Comm.
3. **Which causes of death are associated with each cluster?** We will use perform a descriptive analysis of primary cause of death for each cluster
4. **Can we improve identification of multimorbid individuals through the use of linked HES data?** While we have used HES linkage to look at hospitalisation, we have not used it to identify the diseases an individual has. This made sense from the point of view of studying the GP perspective on multimorbidity, but there will be some patients who receive diagnoses in secondary care that do not get entered into GP records. We will use existing HES definitions from <https://www.caliberresearch.org/portal/phenotypes> . We will assess the prevalence of each of the broad disease areas (from the original protocol) and whether it increases with the addition of HES-only diagnoses. We may also repeat the Latent Class Analysis to see how/if results change.
5. **Do we see similar patterns of multimorbidity in non-HES linked practices?** The non-HES linked practices, often from Scotland, Wales or Northern Ireland, are expected to have similar multimorbidity clusters to England, but there may be some differences. We will re-run our Latent Class Analysis in the non-HES linked practices to assess this.

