**Appendix 1: List of the 36 disease conditions to be included in multimorbidity count**

| Code | Condition | *Criteria* |
| --- | --- | --- |
|  |  |  |
| HYP | Hypertension | *Read Code ever recorded* |
| DEP | Depression and Anxiety | *Read code recorded in last 12 months OR >=4 anti-depressant prescriptions (excluding low dose tricyclics) in last 12 months OR >=4 anxiolytic/hypnotic prescriptions in the last 12 months* |
| PNC | Painful condition | *>=4 POM analgesics in last 12 months OR >= 4 specified anti-epileptics in the absence of an epilepsy Read code in last 12 months* |
| AST | Asthma (currently treated) | *Read code ever recorded AND any asthma prescription in the last 12 months.* |
| CHD | Coronary heart disease | *Read Code ever recorded* |
| DIB | Diabetes | *Read Code ever recorded* |
| THY | Thyroid disorders | *Read Code ever recorded* |
| RHE | Rheumatoid arthritis, other inflammatory polyarthropathies & systematic connective tissue disorders | *Read Code ever recorded* |
| HEL | Hearing loss | *Read Code ever recorded* |
| COP | COPD | *Read Code ever recorded* |
| IBS | Irritable bowel syndrome | *Read code ever recorded OR ≥ 4 prescription only medicine antispasmodic prescription* |
| CAN | New diagnosis of cancer in last five years | *Read code first recorded in last 5 years* |
| ALC | Alcohol problems | *Read Code ever recorded* |
| OPS | Other psychoactive substance misuse | *Read Code ever recorded* |
| CON | Constipation (Treated) | *≥4 laxative prescriptions in last year* |
| STR | Stroke & transient ischaemic attack | *Read Code ever recorded* |
| CKD | Chronic kidney disease | *Best of the last 2 GFR readings <60* |
| DIV | Diverticular disease of intestine | *Read code ever recorded* |
| ATR | Atrial fibrillation | *Read code ever recorded* |
| PVD | Peripheral vascular disease | *Read code ever recorded* |
| HEF | Heart failure | *Read code ever recorded* |
| PRO | Prostate disorders | *Read code ever recorded* |
| EPI | Epilepsy (currently treated) | *Read code ever recorded AND antiepileptic prescription in last 12 months* |
| DEM | Dementia | *Read code ever recorded* |
| SCZ | Schizophrenia (and related non-organic psychosis) or bipolar disorder | *Read code ever recorded/recorded in last 12 months OR Lithium prescribed in last 168 days* |
| PSO | Psoriasis or eczema | *Read code ever recorded AND ≥ 4 related prescriptions in last 12 months (excluding simple emollients)* |

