| IBD | Inflammatory bowel disease | *Read code ever recorded* |
| MIG | Migraine | *≥ 4 prescription-only anti-migraine prescriptions in last year* |
| BLI | Blindness and low vision | *Read code ever recorded* |
| SIN | Chronic sinusitis | *Read code ever recorded* |
| LEA | Learning disability | *Read code ever recorded* |
| ANO | Anorexia or bulimia | *Read code ever recorded* |
| BRO | Bronchiectasis | *Read code ever recorded* |
| PRK | Parkinson’s disease | *Read code ever recorded* |
| MSC | Multiple sclerosis | *Read code ever recorded* |
| CLD | Chronic Liver Disease and Viral Hepatitis | *Read code ever recorded* |

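### The ranking of which disease was recorded first (Amendment 4, item 2) puts cancer late by construction, and painful condition, constipation and migraine late if they are dated from their qualifying prescriptions

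*Protocol*

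**What the plan says.** Item 2 of Amendment 4 (Data/Statistical Analysis) asks which conditions are recorded first within each latent class cluster. The first step is a firm plan: "We will begin with a simple descriptive analysis of which diseases within a cluster are (on average) recorded first". A pairwise step, giving temporal order and relative risk for pairs of conditions, may follow but is optional.

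The conditions come from the clustering work: "Our existing clusters are based on the prevalence of conditions in 2012, defined in the following way". The amendment then points to an external code list (v11), which is not reproduced. Item 2 gives no rule for which record supplies a condition's date and no caveat about look-back.

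The only case definitions in the document are in Appendix 1. Most conditions there need a Read code recorded at any time. The ones that matter here are:

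- **Cancer (CAN):** "Read code first recorded in last 5 years".
- **Constipation (CON):** "≥4 laxative prescriptions in last year".
- **Migraine (MIG):** "≥ 4 prescription-only anti-migraine prescriptions in last year".
- **Painful condition (PNC):** at least 4 analgesic prescriptions, or at least 4 of specified anti-epileptics without an epilepsy code, in the last 12 months. No diagnosis code is listed.
- **Depression and anxiety (DEP):** a code, or at least 4 relevant prescriptions, in the last 12 months.
- **Chronic kidney disease (CKD):** "Best of the last 2 GFR readings <60".

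**The concern.** A definition that settles whether a patient has a condition at one date need not say when the condition began. Item 2 takes definitions with very different look-backs and ranks the conditions by time. A condition whose qualifying record must be recent is then compared with conditions whose record may be decades old.

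The output is a statement about sequence: which diseases tend to open a cluster and which come later. For the conditions with short windows, a late position could come entirely from the window. A reader of the published ranking could not tell whether cancer, pain, constipation or migraine comes late because of how disease accumulates or because of how cases were selected or dated. The same distortion would carry into the pairwise step if it is done.

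**Working it through.** The plan gives no figure for this analysis, so there is none to reproduce.

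**1. Sort the Appendix 1 criteria by the date they can yield.**

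| Type of criterion | Conditions | Number |
|---|---|---|
| Read code at any time | most of the list | 25 |
| Code at any time, or prescriptions with no stated window | irritable bowel syndrome | 1 |
| Code at any time combined with a recent-treatment or recent-code element | asthma, epilepsy, psoriasis or eczema, schizophrenia or bipolar disorder | 4 |
| First code must be recent (5 years) | CAN | 1 |
| Prescriptions only, last year | PNC, CON, MIG | 3 |
| Code or prescriptions, last 12 months | DEP | 1 |
| Latest two readings, no calendar window | CKD | 1 |

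The total is 25 + 1 + 4 + 1 + 3 + 1 + 1 = 36. The first three rows (30 conditions) have a route to a date outside any window.

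**2. Ask, for each windowed condition, whether the window selects the cases or only tests current status.**

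- CAN: the window acts on the first record itself. Every included case has its first code within 5 years, so taking the first code ever returns that same recent date. No dating rule changes this.
- PNC, CON, MIG: the window tests current status. Earlier prescriptions may exist, but the stated definition refers only to the last year and offers no code to fall back on. They rank late if dated from the qualifying records.
- DEP: a patient who qualifies on a recent code may have a first code from long before, and that date can be used. The risk arises only if the status criterion supplies the date.
- CKD: the latest readings show current status, not onset. The risk is again conditional, and no calendar window applies.

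**3. Count the pairs touched by CAN, PNC, CON and MIG.**

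- All pairs: 36 × 35 / 2 = 630.
- Pairs with none of the four: 32 × 31 / 2 = 496.
- Pairs with at least one: 630 − 496 = 134, and 134/630 = 21%.
- Breakdown: 4 × 30 = 120 pairs with a condition that has an unwindowed route; 4 × 2 = 8 with DEP or CKD; 4 × 3 / 2 = 6 among the four themselves.
- Cancer alone enters 35 pairs. The other 134 − 35 = 99 involve PNC, CON or MIG without cancer.

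**4. Illustrate the shift.** The documents give no onset data. Assume two conditions with independent onsets, uniform over the H years before the status date, so that each is truly later in 50% of patients. If one condition's date is confined to, and uniform over, the last W years, its mean distance from the status date is W/2, and

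P(windowed condition appears later) = 1 − W/(2H).

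| H (years) | W = 5 (cancer) | W = 1 (12-month dating) |
|---|---|---|
| 10 | 1 − 5/20 = 75% | 1 − 1/20 = 95% |
| 20 | 1 − 5/40 = 87.5% | 1 − 1/40 = 97.5% |
| 30 | 1 − 5/60 = 92% | 1 − 1/60 = 98% |

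Simulating 1,000,000 pairs of onsets per row agrees to within about 0.2 percentage points. The figures describe a windowed condition set against one with an open history, which is the case for the 120 pairs above. They do not apply to pairs that share a window, such as CON with MIG, or to CKD.

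**The case against.** The strongest reply is that the Appendix 1 windows decide who counts as a case in 2012, and nothing says they also set the date. The ordinary meaning of recorded first is the earliest entry in the history. On that reading item 2 merely leaves out a dating rule, which an analysis plan could supply. The reply also notes that the list in force is the external one: Amendment 4 speaks of "a list of ~40 conditions", while the appendix is headed "List of the 36 disease conditions to be included in multimorbidity count".

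Much of this stands. A reader might infer that all six conditions with a recent-status criterion are necessarily dated late, or that the whole disease order is an artefact. The documents support neither. DEP can be dated from an earlier code, CKD has no calendar window, and order among the 30 conditions with an unwindowed route is untouched. Nor does item 2 state a hypothesis that the ranking would test; it is descriptive.

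Two things survive. For cancer the reply fails, because the window acts on the first record and so selects the cases; a dating rule added later cannot undo that. For PNC, CON and MIG the earliest-entry reading has no defined entry to look for, since Appendix 1 lists no code and refers only to the last year. Carrying Appendix 1 over to the v11 list is an assumption. It is a reasonable one, because item 4 of the same amendment refers back to the disease areas of the original protocol and no other definitions are given.

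**Conclusion.** The point holds for four conditions. If the v11 list keeps the Appendix 1 criteria, cancer ranks late in item 2 under any dating rule, and PNC, CON and MIG rank late if dated from their qualifying prescriptions. Together they enter 21% of pairs. DEP and CKD are at risk only if they are dated from the status criterion instead of the first qualifying record.

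Where the effect applies it is large, but the percentages are illustrative. They rest on independent, uniform onsets over an assumed 10 to 30 years, and the 12-month figures also assume dating within the window. The point concerns the position of the affected conditions in a secondary descriptive analysis. It does not touch the prevalence estimates or the clusters themselves.

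**What to change.** Add a paragraph to item 2 that sets onset dates separately from the 2012 status criteria:

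- **Code-based conditions, including DEP:** the first code ever recorded.
- **Cancer:** re-ascertain cases without the 5-year limit for this analysis only, leaving cluster membership as it is, or leave cancer out of the ranking. Using the first code ever among the present cases changes nothing.
- **PNC, CON, MIG:** the first date on which the prescription criterion was met in any rolling 12 months of the record.
- **CKD:** the first qualifying low readings.
- **Comparison:** compare order only within the span of record in which both conditions could have been observed. This matters because Study Design requires only 12 months of registration before January 1, 2012, so the usable history may be short for some patients.
- **Reporting:** flag or omit any condition that cannot be dated this way, and state which v11 criteria were used.

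The cost is this paragraph and extra programming on records already held. The downside is fewer patients with a usable order for the prescription-defined conditions.
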